#### Analysis of sociodemographic data and treatment expectations

2.7.1

Sociodemographic characteristics and treatment expectations will be assessed, with data stratified by age (younger adults: <65 years; older adults: ≥65 years) to account for potential variations in acceptance and efficacy of herbal medicine across age groups. Continuous variables will be reported as mean ± standard deviation or median (interquartile range) and compared using Student’s t-test or nonparametric tests for non-normal data, with age-stratified subgroup analyses. Categorical variables will be presented as frequencies (%) and compared using chi-squared or Fisher’s exact test, incorporating age stratification to enhance generalizability.

#### Analysis of efficacy endpoints

2.7.2

1) Primary efficacy endpoint

Changes in Numeric Rating Scale (NRS) for radiating pain and Oswestry Disability Index (ODI) from baseline to week 7 will be analyzed using a Linear Mixed Model, with group as a fixed factor and relevant baseline covariates. Missing data will be handled via Mixed Model for Repeated Measures (MMRM), with sensitivity analyses using ANCOVA on datasets imputed by multiple imputations (MI) and Last Observation Carried Forward (LOCF).

2) Secondary efficacy endpoints

Changes in NRS for low back pain, 100 mm Pain Visual Analog Scale (VAS), Roland-Morris Disability Questionnaire (RMDQ), EuroQol 5-Dimension 5-Level (EQ-5D-5L), Health Information National Trends Survey (HINT-8), Global Perceived Effect (GPE), Patient Health Questionnaire-15 (PHQ-15), economic measures, and Kidney Yin Deficiency Pattern Identification Questionnaire (DSKI) scores will be analyzed using a Linear Mixed Model with baseline covariates. Missing data will be managed via MMRM, with ANCOVA sensitivity analyses using MI and LOCF. Non-inferiority testing, with margins of −1.75 (NRS) and −10 (ODI), will be conducted if superiority is not achieved, considering herbal medicine non-inferior if the 95% confidence interval lower bound does not exceed these margins.

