**Methods:**

This pragmatic randomized controlled trial will be a two-arm parallel study designed to evaluate the effectiveness and safety of herbal medicine therapy for low back pain and radiculopathy resulting from lumbar intervertebral disc herniation. Seventy-four eligible adult participants, aged 19 years or older, with magnetic resonance imaging or computed tomography confirmed disc bulging or worse and a Numeric Rating Scale score for radiating pain between three and six, will be randomly assigned to either the herbal medicine strategy treatment group or a usual traditional Korean medicine treatment group that excludes herbal medicine. The primary outcomes will be changes in the Numeric Rating Scale for radiating pain and the Oswestry Disability Index at week seven. Secondary outcomes will include various pain, disability, quality of life, and economic evaluation measures assessed at multiple time points up to 26 weeks. Safety will be continuously monitored through adverse event reporting, laboratory tests, and vital signs. Statistical analysis will primarily use intention-to-treat and per-protocol populations, employing linear mixed models for efficacy endpoints and chi-squared or Fisher’s exact tests for safety data. Non-inferiority testing will be performed if superiority is not established.

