### Sample size calculation

2.3

The target sample size for this PRCT was rooted on a previous research (17). The required sample size was determined by calculating the minimum number of participants needed to detect a clinically meaningful difference between the intervention and control groups, specifically for the primary outcome measure, using a superiority design. The effect size (Cohen’s d) was estimated at 0.5, representing a moderate difference we aimed to detect. Assuming an alpha level (*α*) of 0.05 (two-sided) and a statistical power (1 − *β*) of 80% (0.80), the required number of participants per group (n) was calculated using the formula for comparing two independent means: *n* = 2 × *δ*2(Zα/2 + Zβ)2 × *σ*2, where Zα/2 and Zβ are the standardized normal deviates corresponding to the significance level and power, σ is the estimated standard deviation, and δ is the minimum clinically important difference. We estimated the standard deviation (σ) to be 10 points and set the minimum detectable difference (δ) to be 5 points on the primary outcome scale. Accounting for an anticipated 15% attrition rate, the total required sample size was adjusted from N_calculated_ to N_final_ to ensure adequate power at the study’s conclusion, resulting in a target enrollment of 74 participants (37 per group). Target sample sizes are listed in Table 2. This trial is powered for a superiority outcome, but a secondary, exploratory non-inferiority (NI) analysis is planned to assess the comparative effectiveness or safety of the intervention if the superiority hypothesis is not met. This approach is clinically relevant for pragmatic trials, evaluating whether the intervention is “not worse” than the control within a predefined NI margin (*Δ*). However, the sample size of 74, calculated for superiority, is likely insufficient for a definitive NI trial, as NI analyses typically require larger samples to ensure the confidence interval of the treatment difference lies within Δ. To address this, the manuscript will clarify that the NI analysis is exploratory and hypothesis-generating, underpowered for this endpoint, and will report the NI margin and two-sided 95% confidence interval for the primary outcome difference.

**Table 2 tab2:** Target sample size of the study.

Category	Control group	Intervention group	Total participants
Efficacy evaluable cases	33	33	66
Total sample size (incl. 10% dropout)	37	37	74

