### Outcome measures

2.6

This study used a comprehensive set of outcome measures to evaluate the effectiveness and safety of the interventions. All patient-reported outcomes were assessed at specific visits throughout the study.

(1) NRS scores for pain intensity (low back and radicular pain).

At weeks −1 (baseline), 0, 3, 5, 7, 12, 19, and 26, participants will assess their low back pain and radiating leg pain over the past week using an 11-point Numeric Rating Scale (NRS), ranging from 0 (no pain) to 10 (worst pain imaginable), selecting the number that best reflects their current discomfort level.

(2) Oswestry disability index.

At weeks 0, 3, 5, 7, 12, 19, and 26 visits, participants will complete the ODI (19) questionnaire by providing answers to each question.

(3) VAS score for pain intensity (low back and radicular pain)

At weeks 0, 7, 12, 19, and 26, participants will use a 100 mm Pain Visual Analog Scale (VAS) (20) to quantify their LBP experienced over the past week. Participants will indicate their current pain level by marking a point on a 100 mm Visual Analog Scale (VAS), ranging from “no pain” to “worst pain imaginable”.

(4) Roland-Morris disability questionnaire (RMDQ)

At weeks 0, 7, 12, 19, and 26, the participants will complete the Roland-Morris Disability Questionnaire (RMDQ) (21) by answering each question.

(5) EuroQol-5 dimension-5 level (EQ-5D-5L)

At Weeks 0, 3, 7, 12, 19, and 26, the participants will complete the EQ-5D-5L (22) questionnaire by responding to each question.

(6) Health-related quality of life instrument with eight items (HINT-8)

At weeks 0, 3, 7, 12, 19, and 26, participants will complete the HINT-8 questionnaire (23). Participants will assess their health status over the past week by selecting one of four response levels for each question, ranging from 1 (e.g., “not at all” for climbing stairs or “not at all depressed” for depression) to 4 (e.g., “unable to climb” or “always depressed”).

(7) Global perceived effect (GPE)

At weeks 3, 7, 12, 19, and 26, participants completed the Global Perceived Effect (GPE) questionnaire (24) by providing answers to each question.

(8) Patient health questionnaire-15 (PHQ-15)

At weeks 0, 7, 12, 19, and 26, participants will complete the Korean version of the Patient Health Questionnaire-15 (PHQ-15). This tool, a 15-item condensed version (25) developed by Kroenke et al. from Spitzer et al.’s PHQ (26), assesses general health status and subjective somatic symptoms.

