### Statistical analysis

2.7

Data will be analyzed using intention-to-treat (ITT) and per-protocol (PP) sets. The ITT population includes all randomized participants receiving at least one dose of herbal medicine or one traditional Korean medicine (TKM) session. The PP population comprises ITT participants with ≥70% herbal medicine compliance or ≥7 TKM sessions. Efficacy outcomes will be assessed in both ITT and PP populations, with ITT as the primary analysis and PP as supportive. Demographic and safety evaluations will use the ITT population, with safety analyses based on raw data without imputation. Statistical analyses will be conducted using SAS version 9.4 (SAS Institute, Cary, NC, United States) with a two-sided significance level of 0.05 and 95% confidence intervals.

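### Two primary outcomes share one 0.05 level with no success rule, and the single sample-size calculation neither fits the NRS nor yields 80% power at 33 per arm

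*Protocol article*

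**What the plan says.** The abstract of the protocol article names two primary outcomes: "The primary outcomes will be changes in the Numeric Rating Scale for radiating pain and the Oswestry Disability Index at week seven". Section 2.1 repeats the pair, and section 2.7.2 analyses both with a linear mixed model ("Changes in Numeric Rating Scale (NRS) for radiating pain and Oswestry Disability Index (ODI) from baseline to week 7 will be analyzed"), although its sub-heading is singular. Section 2.7 sets the level once for all analyses, "with a two-sided significance level of 0.05 and 95% confidence intervals". No section splits alpha, orders the two tests, or says whether one or both must succeed.

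Section 2.3 gives a single calculation, "specifically for the primary outcome measure, using a superiority design", with an alpha "of 0.05 (two-sided) and a statistical power" of 80% and Cohen's d of 0.5. It takes an SD of 10 points and "set the minimum detectable difference (δ) to be 5 points on the primary outcome scale", without naming the scale. Table 2 shows 33 evaluable per arm and 37 enrolled per arm.

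Section 2.6 describes the NRS as an "11-point Numeric Rating Scale (NRS), ranging from 0 (no pain) to 10 (worst pain imaginable", and section 2.2.1 admits only radiating-pain scores from 3 to 6. Section 2.7.2 moves to non-inferiority testing when superiority fails, with margins of −1.75 for the NRS and −10 for the ODI. It does not say which outcome's failure starts that step.

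**The concern.** With two primary outcomes, the trial's error rate and power are undefined until success is defined. If a win on either outcome supports the claim, two tests at 0.05 exceed the stated 5%. If both must win, the 80% in section 2.3 is not the probability of success. The same gap leaves the move to non-inferiority open when one outcome wins and the other does not.

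The calculation cannot settle which outcome was meant. Its SD does not fit the NRS, the outcome listed first, and its inputs do not lead to the number planned. Recruitment began on August 1, 2025, treatment is open-label and both outcomes are patient-reported. A success rule chosen after results are known would carry little weight.

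**Working it through.** **Inputs.** Two-sided alpha 0.05, power 80%, difference 5, SD 10 (d = 0.5), 15% attrition in the text of section 2.3, and 10% dropout and 33 evaluable per arm in Table 2. NRS range 0 to 10 (section 2.6) and entry scores 3 to 6 (section 2.2.1). The correlations r between the two test statistics are assumptions; the article gives none.

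**1. The plan's own figure.** I use the standard formula for two independent means, since the fraction may not have survived extraction.
- n = 2 × (1.960 + 0.842)² × 10² / 5² = 2 × 7.849 × 4 = 62.8, so 63 per arm (126 evaluable).
- With 15% attrition: 63 / 0.85 = 74.1, so 75 per arm (150 in total). With 10%: 63 / 0.90 = 70 per arm (140 in total).
- The planned total of 74 is not reproduced. A one-sided test or 70% power still needs 50 per arm. Table 2's 37 follows from 33 / 0.90 = 36.7. At 15%, 33 would become 33 / 0.85 = 38.8, so 39.

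**2. Does SD 10 fit the NRS?** A variable confined to an interval has an SD of at most half its width.
- From a baseline of 3 to 6, change lies between 0 − 6 = −6 and 10 − 3 = +7, so the maximum SD is 13 / 2 = 6.5. A raw 0 to 10 score has a maximum of 5.
- This treats the entry score as the baseline. If the week 0 score could take any value, change could run from −10 to +10. An SD of 10 would then need half the patients to move from 0 to 10 and half from 10 to 0.
- A between-arm difference of 5 is possible but implausible. The largest possible improvement is 3 to 6 points, depending on entry score, and 5 / 1.75 = 2.9 times the plan's own NRS margin.

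**3. Familywise error if either outcome counts.**
- Independent: 1 − 0.95² = 9.75%.
- Bivariate normal, 1 − P(|Z₁| < 1.96, |Z₂| < 1.96): 9.1% at r = 0.5 and 8.3% at r = 0.7.

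**4. Power with 33 per arm and d = 0.5.** The mean of the test statistic is 0.5 × √(33/2) = 2.031.
- One outcome at 0.05: Φ(2.031 − 1.960) = Φ(0.071) = 53%.
- One outcome at 0.025: Φ(2.031 − 2.241) = Φ(−0.210) = 42%.
- Both at 0.05: 0.528² = 28% at r = 0, 36% at r = 0.5 and 40% at r = 0.7.
- Effect for 80% power at 0.05: 2.802 × √(2/33) = 0.69.

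**5. How much of the shortfall comes from having two outcomes?** At the 63 per arm that the inputs require, power for both is 64%, 69% and 71% at r = 0, 0.5 and 0.7. At r = 0, requiring both takes 80% to 64%, and planning 33 instead of 63 takes 64% to 28%. At r = 0.7 the steps are 80% to 71% to 40%.

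**The case against.** - **Multiplicity rules often sit in the analysis plan, which is not shown.** That is fair, and the 0.05 level for each outcome is inferred from a general sentence that nothing modifies. But the article itself makes a step depend on superiority failing and claims 80% power. Neither statement has a definite meaning with two primary outcomes and no rule.
- **A reader might infer that the trial's type I error is inflated.** The article does not support that outright. Inflation arises only if either outcome can carry the claim, and no section says so. If both are required, error is controlled and the loss is in power.
- **A reader might infer that the difference of 5 is also impossible on the NRS, or that the NRS was not sized at all.** Neither follows. Only the SD is impossible; the difference is merely implausible. Cohen's d of 0.5 is scale-free and could apply to either outcome. What is missing is a difference and SD in NRS points.
- **A reader might blame the 28% to 40% on the two outcomes.** Much of the shortfall comes from the gap between 63 and 33 per arm, which already leaves one outcome at about 53%.
- **A reader might take 5 and 10 to be ODI figures.** By elimination only the ODI could carry them, but section 2.3 does not say so, and the study it cites is not at hand. Labelling the calculation as ODI would also keep one that does not give 33.
- **Baseline adjustment could recover power.** If the SD of 10 is unadjusted, a correlation of about 0.69 with baseline covariates would bring the need to 62.8 × (1 − 0.69²) ≈ 33. Section 2.3 claims no such correlation and uses the formula for two independent means.
- **The non-inferiority consequence is limited.** Separate margins make an outcome-by-outcome reading natural, and section 2.3 calls that analysis exploratory. This stands; one sentence would settle it.

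**Conclusion.** The point holds in this form. Two primary outcomes are tested under one blanket 0.05 level with no success rule, so one of the two stated operating characteristics fails whichever rule is meant. If either outcome counts, error is about 8.3% to 9.75% rather than 5%. If both are required, power is about 28% to 40% rather than 80%. Even one outcome alone has about 53%. These figures assume d = 0.5 on each outcome, 33 evaluable per arm, a normal approximation without covariate gain, and correlations from 0 to 0.7.

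Separately, the SD of 10 cannot describe NRS change from entry scores of 3 to 6. The calculation therefore leaves unnamed the outcome it sized and gives the NRS only a scale-free effect size. How 33 per arm was reached cannot be determined from the article.

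**What to change.** Before any outcome data are seen:

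1. State one success rule. Holm across NRS and ODI is one choice: the smaller p-value at 0.025, then the other at 0.05. Requiring both, or a fixed order, is equally coherent, and the choice is the sponsor's.
2. State that the exploratory non-inferiority step applies to each outcome separately, when that outcome fails superiority.
3. Name the outcome to which the difference of 5 and SD of 10 apply, and give a difference and SD for NRS and ODI separately.
4. Replace the 80% claim with the power that 33 per arm delivers for each outcome under the chosen rule, and use one dropout rate.

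The change is wording, but each rule has a price. At d = 0.5 and 33 per arm, power at Holm's first step (0.025) is about 42% for a given outcome. Requiring both gives 28% to 40%. A fixed order keeps about 53% for the first outcome and tests the second only if the first succeeds.

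Keeping 80% at d = 0.5 with 15% attrition would take a larger trial: 77 evaluable per arm (91 enrolled, 182 in total) for a given outcome at 0.025, or 83 per arm (98 enrolled, 196 in total) if both are required and independent. If enrolment stays at 74, the article should say that 33 evaluable per arm has 80% power at 0.05 only for d of about 0.69.

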This investigation is designed as a pragmatic randomized controlled trial (PRCT) to provide information relevant to decision-making in real-world clinical practice. Unlike explanatory clinical trials, which are typically conducted for drug approval and assess the efficacy of an intervention under ideal conditions, PRCTs evaluate the “overall effectiveness” of a treatment in routine clinical settings (12). It is crucial to understand that PRCTs are not alternatives to traditional randomized clinical trials (RCTs) but rather extensions of explanatory trials (13). Guidelines such as the CONSORT extension checklist and the pragmatic-explanatory continuum indicator summary (PRECIS)-2 are recommended for reporting and evaluating PRCTs (14). A key characteristic of PRCTs is their reflection of actual clinical environments, indicating that treatments and interventions adhere to usual clinical practice, and management methods maintain the same level as real-world care (15).

Numerous clinical studies have adopted this research design, with a notable example being a trial comparing surgical strategies with intensive rehabilitation in patients with chronic LBP. In this study, the PRCT design allowed the use of various surgical methods applicable at each site, determined at the physician’s discretion, without predefining the surgical approach (16). PRCTs are particularly appropriate for evaluating the comparative effectiveness of herbal medicine in treating LIDH, as they enable assessment of interventions under routine clinical conditions and facilitate comparisons where placebo controls are ethically or practically challenging. Despite differences between the experimental arm (herbal medicine, involving daily oral administration) and the control arm (acupuncture, moxibustion, and blood-letting cupping, delivered in periodic sessions), these variations align with standard TKM practice, in which treatment modalities are tailored to individual patient needs and clinical discretion, thereby strengthening the study’s external validity and real-world relevance. To safeguard internal validity and enhance interpretability, the analysis will employ intention-to-treat principles, covariate adjustment for baseline imbalances, sensitivity tests for adherence and frequency variations, and subgroup analyses to explore the influence of modality-specific factors on outcomes, yielding a rigorous and transparent comparison of treatment effects.

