#### Missing value management

2.7.5

Missing data for primary and secondary outcomes will be managed using LOCF imputation, selected for its conservative approach in estimating treatment effects post-dropout, assuming stable participant conditions after the last observation, ensuring robust and interpretable efficacy results.

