### Dropout and withdrawal

2.8

Participants may withdraw voluntarily at any point or be removed by the investigator, with the main reason recorded. Those exiting before treatment begins count as screening failures and, barring medical need, need not complete discontinuation evaluations. Withdrawals due to adverse events (AEs) will receive suitable care, and monitoring will persist for intervention-related AEs until resolved or stabilized. Exclusion criteria include: (1) participant or legal representative requesting withdrawal or revoking consent; (2) newly identified conditions impacting study results; (3) major breaches of inclusion/exclusion rules; (4) confirmed pregnancy; (5) a serious AE necessitating withdrawal or making involvement impractical; (6) barriers to conducting medical or traditional Korean medicine (TKM) procedures for lumbar disc herniation; (7) investigator judgment that ongoing participation is unsuitable; or (8) herbal medicine adherence below 70% across 5 weeks or fewer than six usual care sessions attended. Follow-up assessments may proceed with consent after treatment ends.

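### The named missing-data sensitivity analyses cannot reliably show how much worse drop-outs would have to be to overturn the week-7 result, and LOCF is not reliably conservative

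*Protocol article*

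**What the plan says.** Section 2.7.2 of the protocol article states that changes in radiating-pain NRS and in ODI "from baseline to week 7 will be analyzed using a Linear Mixed Model, with group as a fixed factor and relevant baseline covariates". On incomplete outcomes it then says: "Missing data will be handled via Mixed Model for Repeated Measures (MMRM"). The checks on that approach are named in the same sentence: "with sensitivity analyses using ANCOVA on datasets imputed by multiple imputations (MI) and Last Observation Carried Forward (LOCF"). It gives no imputation model and no range of departures from the main assumption.

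Section 2.7.5 says something different: "Missing data for primary and secondary outcomes will be managed using LOCF imputation". It explains that this method was "selected for its conservative approach in estimating treatment effects post-dropout" and describes the premise behind it as "assuming stable participant conditions after the last observation".

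Section 2.8 lets participants be removed for, among other reasons, serious adverse events, investigator judgement, or adherence below a threshold defined separately for each arm. Assessment after that is optional: "Follow-up assessments may proceed with consent after treatment ends".

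The only other related work is in the Background, which promises "sensitivity tests for adherence and frequency variations", and in section 2.7, which adds a supportive per-protocol analysis. Neither concerns the outcomes of patients whose week-7 value is missing.

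**The concern.** A missing-data sensitivity analysis should vary the assumption on which the main analysis rests. MMRM is valid if missing week-7 values behave like those of comparable patients who stayed. ANCOVA after plain MI makes the same assumption, so agreement between the two says little about robustness. LOCF does vary the assumption, but through a single scenario in which nothing changes after the last contact.

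Informative loss is plausible here. The trial is open-label, the primary outcomes are patient-reported, removal criteria differ by arm, and later follow-up is optional. If the three analyses agreed, a reader could take that as evidence against bias from drop-outs doing worse, although the set does not test that over any range. The Discussion already counts the handling of missing data as a strength.

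**Working it through.** **Inputs.** From section 2.3: SD 10, difference 5, 33 evaluable per arm, and two drop-out figures (15% in the text, 10% in Table 2). From section 2.7.2: margins of 1.75 (NRS) and 10 (ODI). Assumed here: drop-outs 5–10 points worse than predicted, and the observed differences and mean changes used below. Section 2.3 does not say which primary outcome its SD and difference belong to. Reading them as ODI points is an assumption, made because an SD of 10 is implausible on a 0–10 NRS.

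**Plan's own figures.** The plan gives no robustness figure to reproduce. Its inflation step, 33 / 0.90 = 36.7, rounds up to 37 and matches Table 2. With the 15% in the text it would be 33 / 0.85 = 38.8, or 39. Both drop-out rates are carried forward. (The 33 does not follow from the stated effect size: 2 × (1.96 + 0.84)² × 10² / 5² = 62.7, or 63 per arm with unrounded normal deviates. That is a separate matter. I use 33 because it is the planned evaluable number.)

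**Standard error.** SE = 10 × √(2/33) = 2.46. Two-sided significance at 0.05 needs 1.96 × 2.46 ≈ 4.83 points. This ignores any gain from covariate adjustment and holds the SE fixed as values are shifted.

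**Shift if drop-outs in one arm are worse by delta.** Shift = missing fraction × delta.
- 0.10 × 5 = 0.5 points; 0.5 / 2.46 = 0.20 SE.
- 0.15 × 10 = 1.5 points; 1.5 / 2.46 = 0.61 SE.
- Against the planned 5-point difference, this is 10% to 30%.
- For NRS, a delta of 1.75 gives 0.10 × 1.75 = 0.18 to 0.15 × 1.75 = 0.26 points. No NRS standard deviation is given, so this cannot be put in SE units.

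**Tipping point if only herbal-arm drop-outs are shifted.** Delta = (observed difference − 4.83) / missing fraction, computed with the unrounded threshold.

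| Observed difference | 10% missing | 15% missing |
|---|---|---|
| 5 | 1.7 | 1.2 |
| 6 | 11.7 | 7.8 |
| 7 | 21.7 | 14.5 |

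A result near the planned effect is fragile and one 2 points larger is not. No named analysis tells the reader which case applies.

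**Is LOCF conservative?** Assume mean changes of −15 (herbal) and −10 (control), a difference of −5 under missing at random, and drop-outs who carry baseline forward. LOCF then shifts each herbal drop-out by 15 points and each control drop-out by 10, so the LOCF difference is −5 + 15 × (herbal loss) − 10 × (control loss).

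| Herbal / control loss | LOCF difference, baseline carried | LOCF difference, half the change already reached |
|---|---|---|
| 15% / 15% | −4.25 | −4.62 |
| 20% / 10% | −3.0 | −4.0 |
| 10% / 20% | −5.5 | −5.25 |
| 0% / 20% | −7.0 | −6.0 |

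The same method shrinks the herbal effect in the first two rows and enlarges it in the last two. Its size also depends on when patients leave. LOCF thus applies an implicit delta set by the drop-out pattern and not by the analyst.

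**The case against.** The strongest reply has four parts.

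**The MI model may be in a document not shown.** An imputation model is a detail that an article can leave to the analysis plan, and delta- or reference-based MI there would answer the point. This limits the claim: a reader might infer that MMRM and MI must agree almost by construction, and the article does not establish that. What the article does fix is the list of analyses and the justification of LOCF as conservative, and both can be judged as written.

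**LOCF is not blind to worse outcomes.** A reader might infer that none of the planned analyses could reveal harm from drop-outs doing worse. That goes too far. When patients are improving, LOCF gives drop-outs worse values than MMRM would. With 20%/10% loss it moves the difference by 2.0 points against herbal medicine, more than the 0.5–1.5 points above. What remains is that it is one scenario, never goes beyond the last recorded value, and can point the other way.

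**If section 2.7.5 governs, LOCF is the main method,** and MMRM and MI do vary its assumption. That is true, and it is why the two sections must be reconciled. Under either reading, no analysis explores a range of worse outcomes.

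**Missing at random may be credible here.** Assessments may continue after treatment ends, and NRS and ODI are also collected at weeks 3 and 5 (Table 1). These values help, but they cannot verify the assumption for patients who do leave.

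A reader might also infer that the non-inferiority fallback is especially exposed. The documents do not support that. Section 2.3 calls that analysis exploratory and underpowered, and a 0.5–1.5 point shift is 5–15% of the 10-point ODI margin.

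**Conclusion.** The concern holds in a limited form. The named analyses cannot reliably show, or locate, how much worse drop-outs would have to be to overturn the week-7 result, and describing LOCF as conservative is not justified. The plausible effect is modest: 0.5–1.5 points, or 0.2–0.6 SE. It decides the conclusion only when the observed difference lies close to the significance threshold of about 4.83 points.

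This rests on plain MI being a missing-at-random imputation, on SD 10 with 33 per arm applying to ODI, on 10–15% missing in one arm, and on an assumed delta of 5–10 points. It does not show that the planned primary analysis is biased, or that LOCF favours herbal medicine in general. The change is worth making because the method is fixed badly and a better one costs little.

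**What to change.** In section 2.7.2, make arm-specific delta-adjusted MI the main missing-data sensitivity analysis for both NRS and ODI, in place of ANCOVA after LOCF. Impute week-7 values under missing at random, then shift the imputed values of drop-outs worse in each arm in turn, for example by 0 to 10 ODI points and 0 to 1.75 NRS points. Report the shift at which the conclusion changes. LOCF may stay as a descriptive supplement.

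For the exploratory non-inferiority analysis, report the tipping point only. A pass/fail rule at the full margin would be too strict for its stated purpose.

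In the same edit, remove the claim in section 2.7.5 that LOCF is conservative, and state in both sections which method is the main one, since section 2.7.2 names MMRM and section 2.7.5 names LOCF.

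The cost is a few sentences and a short extension of the MI program already planned. The drawback is that the result may be shown to be less robust than the present set would suggest.
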